#### Feedback alone intervention

The feedback intervention will take the form of a summary sheet that presents the results of a set of performance indicators extracted from administrative databases currently available to INESSS. The choice of the indicators for the summary sheet emerged from a consensus between policy makers, managers, healthcare professionals and patients. Quality indicators were produced using data from the Institut national de santé publique du Québec and INESSS, the latter having access to 11 linked health administrative databases. These indicators present a portrait of a specific clientele care (e.g. diabetes or COPD) at the local service network level, the integrated centre level, and the provincial level to allow comparison. A local service network is an integration of health and social services in a given territory responsible to provide a set of services for the population of that specific territory. Integrated centres are usually composed of a few local service networks. The feedback summary sheet will be developed in collaboration between INESSS and the research team. It can be used by the integrated centres to analyze current practices and identify local or regional QI needs. It will be sent to all directors of participating institutions as well as to relevant middle managers and chiefs of all family medicine groups in the region. For the control group, no further QI support will be provided.

#### COMPAS+ quality improvement collaboratives

For each integrated centre receiving the COMPAS+ intervention, reflective practice workshops will be offered in three local service networks. For each local service network, it is expected that approximately 30 people will participate in the COMPAS+ workshop (managers, health professionals, patient partners) and that, after the workshop, a local QI project implementation committee will be set up to implement action plan(s).

The COMPAS+ QICs will be conducted in three phases: 1) a preparatory phase, 2) a workshop phase, and 3) QI project follow-up phase.

##### 1) Preparatory phase

During this phase, INESSS will obtain formal support for the COMPAS+ program from integrated healthcare organization directors and help from local implementation committees within this organization to encourage strong and sustained local leadership before and after QI reflective workshops. Local implementation committees (managers, health professionals and patient partners) will facilitate the organization of workshops, participant recruitment, and QI project implementation and monitoring. Primary care teams – consisting of family physicians, nurses, other professionals, and managers of the same local service network – will be invited to participate in the QI reflective workshop, as will three or more patient partners living with the targeted chronic disease.

##### 2) QI reflective workshop

The workshop will feature three core QI components: 1) A tailored feedback intervention that includes a population-based performance assessment and comparison to best practices outlined in clinical practice guidelines; 2) Critical reflection exercises in large and small groups to promote reflection around the selected quality indicators; 3) A collaborative problem solving and action planning process involving small groups of 8–10 people that identify priority problems, propose actionable solutions, and negotiate the content of their QI action plans. External experts in QI and change management working with INESSS will facilitate the workshops, share information about best practices in QI and chronic disease care, and guide participants through the workshop’s QI activities. Patient partners will actively participate to the workshop and help shape the teams’ QI action plans. In order to properly support the patient partners during the process, a patient coach partner will meet with patient partners during their preparatory training prior to the workshop and provide guidance, encouragement, and role modelling during the workshop.

##### 3) QI project follow-up phase

After the workshop, the local implementation committee will meet with an INESSS QI team a minimum of four times over the next 18 months to finalize or refine local QI action plans and review progress with the implementation of QI projects. These meetings will actively engage local committees in the appropriate use of the Model for Improvement and use (a) active facilitation strategies to clarify QI objectives and activities and facilitate repeated small-scale improvement cycles, and (b) process control charts - a visual tool that displays objectives, indicators, activities and responsibilities - are used to support the team [45].

#### Outcomes measures

To assess the effectiveness of the COMPAS+ QICs, we will use three main measures of primary care quality easily retrievable from INESSS’s health administrative databases: [1] the number of emergency visits for ambulatory care sensitive conditions, a widely used measure of primary care accessibility and quality [46, 47], [2] number of patients visiting five or more different physicians over a period of twelve months, because it is an indicator of how formal the relationship between a family physician and a patient is (patient rostering has been recognized as an important feature of a high-performing primary care system) [48–50]; and [3] persistence to medication regimens over a period of twelve months, since poor adherence compromises effectiveness of treatment and health of patients at risk of chronic disease complications [51, 52].

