#### Interrupted time series power calculation and analysis

The lack of estimates for some parameters required for the calculation of an ITS study sample precludes the calculation of a precise sample size. However, 36 points of observation (12 months before, 24 months after) should provide > 80% power to detect a significant effect of the intervention on primary outcome measures, assuming an effect size > 0.5 (medium effect or greater), autocorrelation > − 0.1, and a first-order autoregressive segmented regression model with both level (intercept) and trend (slope) changes expected [53]. To isolate the effect of the COMPAS+ QIC on the three quality indicators from other changes that could take place during the study period while adjusting for time, seasonal trends, and random errors, differences between the two study conditions (COMPAS+ or feedback only) will be assessed using linear mixed models for longitudinal data, where individuals’ data observed over time are nested into QICs to take account of the inter-QIC correlation. Descriptive statistics will also be generated for both study groups and all QICs.

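### The 36-point power statement does not carry over to the two main outcomes that are defined over twelve months

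*Protocol article*

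**What the plan says.** The section on outcome measures lists three main measures of primary care quality, all taken from administrative databases:

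- "the number of emergency visits for ambulatory care sensitive conditions", with no accrual window attached;
- "number of patients visiting five or more different physicians over a period of twelve months";
- "persistence to medication regimens over a period of twelve months".

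The section on interrupted time series power and analysis first says that a precise sample size cannot be calculated. It then counts 36 observations, 12 months before and 24 months after, and says that these "should provide > 80% power to detect a significant effect of the intervention on primary outcome measures". The conditions are "assuming an effect size > 0.5 (medium effect or greater"), "autocorrelation > − 0.1", and a first-order autoregressive segmented model with changes in both level and slope. Thirty-six points over 36 months means one point per month.

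The same paragraph names the analysis for all three indicators: linear mixed models on individuals' longitudinal data, nested in collaboratives, comparing COMPAS+ with feedback only. It does not say how a twelve-month measure becomes a monthly point, or how a window that spans the intervention is treated.

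**The concern.** A segmented regression needs each point to belong to one side of the interruption, and needs enough points before it to estimate a trend. A monthly count of emergency visits can meet both needs. A quantity accumulated over twelve months meets neither on a 12 + 24 month calendar, because the whole pre-intervention period is exactly one window long.

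This affects two of the three measures for the first objective, whether COMPAS+ improves care more than feedback alone. The Discussion also presents the number of repeated observations as an advantage over earlier time series studies. For these two outcomes, neither that advantage nor the power figure is established. If overlapping windows were entered as ordinary monthly points, a sudden change would be read as a gradual one and standard errors would be too small.

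**Working it through.** **The plan's own figure.** The power was checked by generalised least squares on an intercept, time, post indicator and time since interruption. The check used 12 + 24 points, one series, AR(1) errors with φ = −0.1 and known variance. Two-sided α = 0.05 is an assumption, since the article states none. The article also does not say whether the 0.5 is a level or a slope, or in which standard deviation.

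| Reading of 0.5 | Power |
|---|---|
| Level change of 0.5 SD | 11% |
| Slope change of 0.5 SD per month | above 99% |
| Slope change reaching 0.5 SD at 24 months | 6% |

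The figure above 80% is reached when the slope changes by 0.5 SD per month, but not on the other two readings. It is neither confirmed nor refuted. The question here is whether it can apply to a twelve-month measure at all.

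**Counting windows.** Inputs: window 12 months; months 1–12 before and 13–36 after.

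- Non-overlapping: 36/12 = 3 values, 1 before and 2 after, for a model with 4 regression parameters.
- Rolling, inside the 36 months: 36 − 12 + 1 = 25 values. The window ending in month 12 is wholly before (1), those ending in months 13–23 straddle (11), and those ending in months 24–36 are wholly after (13).
- A full set of 36 trailing windows: 36 + 11 = 47 months of data. Of the 24 post points, 11 still contain pre-intervention time.
- Forward windows, starting in each month: the 12 pre-intervention cohorts have 0/12, 1/12, …, 11/12 of their time after the interruption, on average 5.5/12 = 46%. The last cohorts need data up to 11 months past month 36.

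**Autocorrelation from overlap.** With independent months, two trailing windows k months apart share 12 − k months, so the correlation is (12 − k)/12. That is 0.917 at lag 1, 0.50 at lag 6 and 0 at lag 12. An AR(1) process with the same lag-1 value has 0.917⁶ ≈ 0.59 at lag 6 and 0.917¹² ≈ 0.35 at lag 12. The value 0.917 satisfies the stated condition, which has no upper bound, but the shape is not AR(1).

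**Smearing, without noise.** A true immediate step of 1.00, seen through 36 trailing windows and fitted by ordinary least squares, comes out as a level change of 0.32 plus a spurious slope of 0.039 per month. Forward windows give a level change of 0.00, a false pre-intervention trend of 0.083 per month and a slope change of −0.083. Dropping the 11 straddling trailing windows leaves 36 − 11 = 25 points and recovers level 1.00 and slope 0.

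**Simulation.** Independent monthly normal noise (an assumption), 12-month rolling means, AR(1) segmented regression, separate simulations of 1,500 to 3,000 series.

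| Quantity | Monthly points | 36 rolling points |
|---|---|---|
| Slope test, rejection of a true null | 7–9% | 33–37% |
| Level test, rejection of a true null | 8–9% | about 12% |
| True 0.5 SD step: mean fitted level | about 0.5 | about 0.05 |
| True 0.5 SD step: mean fitted slope per month | about 0 | about 0.017 |
| True 2 SD step: mean fitted level | 1.99 | 0.18 |
| True 2 SD step: level test rejects | 80% | 18% |

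The difference series, intervention minus control, gave the same null rejection (level 12%, slope 36%). The control arm therefore does not remove the problem under this model.

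**The case against.** Three objections have force.

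- **Data outside the 36 months.** A reader might infer that these outcomes cannot supply 36 monthly points. The documents do not support that. The measures come from administrative databases described as easy to draw on, and 36 trailing values need only 11 additional earlier months. The inference holds only for non-overlapping windows or for data confined to the stated 36 months. Whether earlier months will be extracted is not stated.
- **The stated analysis is a different model.** A reader might also infer that the planned test is invalid for these outcomes. That was shown only for the AR(1) segmented regression, which the article uses in its power statement. The named analysis is a linear mixed model on individual data, and its error rate was not computed. Its measurement interval and error structure may be set in the full protocol or analysis plan, which is not shown.
- **The simulation is a proxy.** A rolling mean of independent monthly values is neither a count of patients crossing a five-physician threshold nor a persistence measure. The plan does not assume an immediate step either: it expects level and slope changes, and follow-up meetings run over 18 months. Smearing alone creates no false effect under the null. The inflated error comes from the overlap, and even clean monthly data gave 7–9% with this estimator.

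These points limit how far the error rates can be taken, but they do not reconcile the two sections. The article itself ties one power figure to all primary outcome measures, and no way of forming the twelve-month values makes that figure apply. The mixed model is open to the same smearing if straddling windows enter as post points.

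**Conclusion.** The concern holds for the power statement. Within the stated calendar, the two twelve-month measures give 3 separate values, or 25 rolling values with 1 wholly before the intervention. With 11 extra months they give 36 values, of which 11 of the 24 post points are mixed and neighbouring values are correlated at 0.92 by construction. On none of these readings does the figure above 80% apply to them.

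The window counts and the 46% follow from the stated windows alone. The 0.92 also assumes independent months. The rejection rate of about 35%, and the fit of a 0.5 SD step as roughly 0.05 plus 0.017 per month, rest on independent monthly noise and an uncorrected AR(1) segmented fit. They do not show that the mixed-model comparison of the arms is invalid. Severity is moderate: the article needs a correction and a definition, and the design need not be abandoned.

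**What to change.** Limit the 36-point power statement to emergency visits. For the other two outcomes, choose one route and state the unit of observation:

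1. Use versions with monthly or quarterly resolution, for example the proportion of days covered per month or distinct physicians per quarter.
2. Keep the twelve-month definition, extract earlier data, exclude windows that straddle the intervention, and model the remaining overlap (for example with a moving-average error structure up to lag 11). Excluding the straddling windows removes the smearing but not the correlation, so both steps are needed.
3. Keep the twelve-month definition and compare complete, non-overlapping years between the arms, with earlier years as baseline. This is optional: on 3 versus 6 centres it gives up information, and its power would need its own check.

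The cost is a change of wording, some earlier data extraction under routes 2 and 3, fewer usable points (25 rather than 36 under route 2 with trailing windows), and no claim of more than 80% power for these two outcomes.

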#### Interrupted time series power calculation and analysis

The lack of estimates for some parameters required for the calculation of an ITS study sample precludes the calculation of a precise sample size. However, 36 points of observation (12 months before, 24 months after) should provide > 80% power to detect a significant effect of the intervention on primary outcome measures, assuming an effect size > 0.5 (medium effect or greater), autocorrelation > − 0.1, and a first-order autoregressive segmented regression model with both level (intercept) and trend (slope) changes expected [53]. To isolate the effect of the COMPAS+ QIC on the three quality indicators from other changes that could take place during the study period while adjusting for time, seasonal trends, and random errors, differences between the two study conditions (COMPAS+ or feedback only) will be assessed using linear mixed models for longitudinal data, where individuals’ data observed over time are nested into QICs to take account of the inter-QIC correlation. Descriptive statistics will also be generated for both study groups and all QICs.

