### Quantitative component: controlled interrupted time series

#### Setting, participants, randomization

Working in collaboration with INESSS, we will invite integrated health and social service centres to participate in the study. These integrated centres are responsible for ensuring accessibility, continuity, and quality across a continuum of health services (primary and specialist care) for the population in their region [44]. Integrated centres include all public healthcare organizations, such as hospitals, local community health and social services centres, long-term care facilities, and rehabilitation centres under a single governing body per territory. There are 22 integrated centres in the province of Quebec. Given that five had already piloted the COMPAS+ program, 17 integrated centres are eligible for this study. Each centre establishes service agreements with medical clinics in their region. Family Medicine Groups (FMGs) are the main model for interdisciplinary team-based primary care, with over 330 FMGs providing care to nearly 80% of the population. These FMGs work in collaboration with other health services provided in the community based on their geographical proximity.

We will identify nine integrated centres and stratify them according to the type of region and the size of the population served (e.g. rural (less than 150,000 inhabitants in the main city), semi-rural (150 to 200,000 inhabitants in the main city) or urban (more than 200,000 inhabitants in the main city)). They will be randomly assigned within strata to one of the two study groups using random assignment generator: 1) *control group* consisting of three centres receiving only a feedback intervention and 2) *experimental group* consisting of six centres receiving the COMPAS+ intervention in addition to the feedback intervention [41].

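### The stated power of over 80% rests on inputs for a segmented time series and is not the power of the planned comparison of six COMPAS+ with three feedback-only centres

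*Protocol article*

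**What the plan says.** The section on power and analysis of the interrupted time series opens with a caveat: "The lack of estimates for some parameters required for the calculation of an ITS study sample precludes" a precise sample size. It then puts power for the primary outcomes above 80% all the same, on the ground that "36 points of observation (12 months before, 24 months after) should provide" it. The conditions are an effect of at least medium size (over 0.5), a lower bound of −0.1 on the autocorrelation, and as the model "a first-order autoregressive segmented regression model with both level (intercept) and trend (slope) changes expected".

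The next sentence of that section describes the analysis: a linear mixed model that assesses the difference between the two study conditions, with individuals' repeated data nested in collaboratives. Objective 1 (Study objectives) asks how far COMPAS+ is more effective than feedback alone. The section on setting, participants and randomization assigns nine integrated centres within strata, six to COMPAS+ plus feedback and a control group "consisting of three centres receiving only a feedback intervention".

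**The concern.** Every condition attached to the power figure describes a segmented regression of a time series: its length, its autocorrelation, and its change in level and trend. The planned test is a contrast between two groups of randomised centres. Its precision also depends on the noise in the control series, on how many centres each arm has, and on how much centres differ from one another in their change over time. None of these appears among the stated conditions.

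The Discussion presents the controlled comparison and the random allocation as strengths, and expects the results to shape wider implementation in the province. If the comparison is null, a reader who takes the 80% at face value may conclude that COMPAS+ adds nothing to feedback, although the plan does not show that its design could detect the effect.

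**Working it through.** **Inputs from the article.** 12 points before and 24 after; effect size above 0.5; autocorrelation above −0.1; six and three centres. **Not given:** the SD to which 0.5 refers, whether it is a level or a slope change, the between-centre variance, and the significance level. Two-sided 0.05 is assumed below.

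**1. The stated figure.** It can be neither confirmed nor refuted, because the effect scale is undefined. For one series with intercept, trend, level change and slope change (36 − 4 = 32 df):
- 0.5 as a level change in monthly SD units: with independent errors, the variance of the level change is 1/12 + 5.5²/143 + 1/24 + 12.5²/1150 = 0.472, so SE = 0.687 and power is 11%. At autocorrelation −0.1 it is 12%.
- 0.5 as a slope change in SD per month: power is 92% to over 99% for autocorrelation from −0.1 to 0.7. This effect amounts to 0.5 × 24 = 12 SD by month 24, which is hard to call medium.

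**2. From one series to a difference of two.** This step needs no effect scale. Suppose one series has exactly 80% power, so effect/SE = 1.960 + 0.842 = 2.802.
- Control series equally noisy: the SE grows by √2. Power = Φ(2.802/1.414 − 1.960) = Φ(0.021) = 51%.
- Control series with twice the variance (three centres against six): the SE grows by √3. Power = Φ(2.802/1.732 − 1.960) = Φ(−0.342) = 37%.

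With t-based degrees of freedom the results are 52% and 38%.

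**3. Six against three centres.** Let s be the SD of the centre-level change (true variation plus sampling noise) on the scale of the 0.5. The SE of the difference is s·√(1/6 + 1/3) = 0.707s. Nine centres less two arm means leave 7 df, with critical value 2.365. The noncentrality is 0.5/(0.707s).

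| s (assumed) | noncentrality | power |
|---|---|---|
| 0.1 | 7.07 | >99% |
| 0.2 | 3.54 | 86% |
| 0.3 | 2.36 | 53% |
| 0.5 | 1.41 | 23% |
| 1.0 | 0.71 | 9% |

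Power reaches 80% at s ≈ 0.216, which is an effect of 0.5/0.216 ≈ 2.3 between-centre SDs of change. If stratification leaves 5 df, the requirement is about 2.5 SDs.

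**The case against.** The article hedges: it says that a precise calculation is not possible and words the power as an expectation. A journal article may also leave the details of a power calculation to the full protocol. The hedge concerns missing parameter values, however. It does not tell the reader that the figure describes a different test. Nor is this a matter of omitted detail, since the article states a power, the model behind it, and then a different analysis.

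A reader might go further and infer that the comparison has only about 10% power. The article does not support that. The low values arise when 0.5 is read in between-centre SDs of change, or as a level change in monthly SDs. It defines neither scale, and the second gives only 11% to 12% even for one series, so it is unlikely to be the scale intended. If centres change alike (s of 0.2 or less), six against three exceeds 80%. Averaging over nine centres can also raise power above that of one series: with no between-centre differences in change, and the level change evaluated at the first post-intervention month, it is 15% against 11% at autocorrelation −0.1.

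It also stands that the single-series origin is inferred from the listed conditions, because the cited source is not available here. And access to databases ("the latter having access to 11 linked health administrative databases") does not mean that variance estimates were to hand at planning. That access matters only for the remedy.

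**Conclusion.** The point holds as a mismatch between the basis of the power figure and the planned contrast. The stated power is not the power of the COMPAS+ versus feedback-only comparison, and nothing in the article shows that this comparison has 80%. This follows from the text alone and needs no assumed parameter.

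The size of the shortfall, or whether there is one, cannot be determined. The 51% and 37% assume exactly 80% on one series and the stated variance ratios. The range from 9% to over 99% depends on the assumed s. What can be said is that 80% power needs an effect of about 2.3 between-centre SDs of change, at 7 df and two-sided 0.05. The autocorrelation condition gives no protection either: it sets only a lower bound, and power falls as positive autocorrelation rises over most of the range.

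**What to change.** Withdraw the statement of over 80% as the power for the primary comparison, or label it a single-series approximation. Replace it with power, or a minimum detectable difference, for the condition-by-time contrast under the planned mixed model with nine centres at 6:3. State:
- the effect scale, and whether it concerns level, slope or their combination;
- a range of between-centre variance in change and of autocorrelation, which historical series in the INESSS databases could supply;
- the small-sample degrees of freedom.

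The cost is a short simulation and probably a less favourable stated figure. No centres need be added and the planned analysis need not change.

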This study has also several strengths. First, we are using an integrated KT approach with a strong, meaningful and sustained engagement from project partners, including clinicians, decision-makers and patient partners. We are also using a mixed methods approach with rigorous quantitative (interrupted time series) and qualitative (multiple case study) components. Much of the previous research on QICs has involved uncontrolled before-after studies that are limited in their ability to mitigate for bias and confounding and consider contextual factors having a potential influence on outcomes targeted by the QIC (Wells et al. 2018). Even when designs like ITS were used, previous studies have lacked enough repeated observations to adequately describe trends in outcomes (Wells 2018). The present study compares COMPAS+ to a feedback only control condition, gathers data through multiple sources at multiple time points before the intervention and for 24 months post-intervention, and adopts a mixed approach to data analysis to ensure a rich understanding of implementation processes and factors contributing to intervention effectiveness. Finally, the random allocation of sites to either the intervention or control conditions is another strength of this research.

Since QICs are increasingly being used and implemented to support QI efforts in healthcare, we expect that the results of this study will produce significant and important knowledge to inform the development and evaluation of future QICs and implementation of innovative chronic disease management strategies.

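### The 12-month baseline is one seasonal cycle; because the outcomes come from administrative databases already in use, 24 to 36 baseline months would sharpen the trend and late-effect estimates, by how much depending on how pre-trends are modelled

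*Protocol article*

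**What the plan says.** The section on ITS power calculation and analysis sets 36 observation points, "12 months before, 24 months after", and says this gives more than 80% "power to detect a significant effect of the intervention on primary outcome measures", "assuming an effect size > 0.5 (medium effect or greater") and "autocorrelation > − 0.1". The power statement rests on a segmented regression with first-order autoregressive errors in which both level and slope may change. The comparison of the two conditions is then made with linear mixed models that adjust for time and season.

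On the data source, the Outcomes measures section speaks of "three main measures of primary care quality easily retrievable" from the INESSS administrative databases. The section on the feedback intervention describes INESSS as "the latter having access to 11 linked health administrative databases". The article does not say how far back these data go, what an extract costs, or why the baseline stops at 12 months.

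**The concern.** In a segmented model the pre-intervention trend supplies the counterfactual. Here a line fitted to 12 points is carried forward over 24 months, twice its own length. Those 12 points are a single year, so a rise within the year may be trend or season, and the model is meant to adjust for both.

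The estimates most exposed are the trend change and the effect late in follow-up. They matter in this trial because support for the local projects runs over 18 months after the workshop (QI project follow-up phase), so any benefit is likely to build gradually. In a prospective study a short baseline saves time and money. With outcomes drawn from existing administrative records, the saving is probably small.

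**Working it through.** **Inputs.** 12 pre and 24 post monthly points, AR(1) errors, level and slope change (ITS power calculation and analysis); six and three centres (Setting, participants, randomization). Assumed: monthly SD 1; autocorrelation ρ from 0 to 0.3, since the article gives only a lower bound; two-sided alpha 0.05, which is not stated.

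**The plan's own figure.** The power above 80% could not be reproduced under the usual readings. A level change of 0.5 SD gives 8.5 to 11% in one series (ρ from −0.1 to 0.5) and 12 to 17% with six against three centres. Only a slope change of 0.5 SD per month exceeds 80%, and that amounts to 0.5 × 23 = 11.5 SD over the follow-up. The unit of the effect size is not given, so the figure is not reproducible rather than certainly wrong.

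**Reading A: each arm or centre has its own pre-trend.** Let n be the number of pre points and S(n) = n(n² − 1)/12, so S(12) = 143, S(24) = 1150, S(36) = 3885. At ρ = 0:

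- Var(trend change) = 1/S(n) + 1/1150.
- Var(level change) = 1/n + ((n + 1)/2)²/S(n) + P.
- Var(month-24 effect) = 1/n + ((n + 1)/2 + 23)²/S(n) + P.
- P is the variance of the post-intervention line at its first or last month: 1/24 + 11.5²/1150 = 0.157.

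For n = 12, the month-24 variance is 1/12 + 29.5²/143 + 0.157 = 0.083 + 6.086 + 0.157 = 6.326, so the SE is 2.52. About 97.5% of this variance (6.169/6.326) comes from extrapolating the baseline line.

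| SE at ρ = 0 | 12 pre | 24 pre | 36 pre |
|---|---|---|---|
| Trend change, per month | 0.089 | 0.042 (−53%) | 0.034 (−62%) |
| Month-24 effect | 2.52 | 1.14 (−55%) | 0.79 (−69%) |
| Level change | 0.73 | 0.58 (−21%) | 0.52 (−29%) |

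At ρ = 0.3 (generalised least squares) the month-24 SE goes 3.08 → 1.48 → 1.05 and the level SE 0.87 → 0.72 → 0.66. Over ρ from 0 to 0.3 the reductions at 24 and 36 months are 50–53% and 60–62% (trend change), 52–55% and 66–68% (month 24), and 17–21% and 24–29% (level). With 36 months the trend-change and month-24 SEs are still more than halved at ρ = 0.7; at ρ = 0.9 that takes about 60 months. For six against three centres each SE is multiplied by √(1/6 + 1/3), so the ratios hold if series length and error structure are the same in both arms.

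**Season.** An annual sine and cosine explain 63% of the variance of a linear trend over 12 points, 16% over 24 and 7% over 36. The SE of a slope fitted to the 12 baseline points alone rises from 0.084 to 0.137 when they are added. With month dummies, 12 points cannot separate trend from season at all. In the full series at ρ = 0, the level SE goes 0.85 → 0.62 → 0.54 with the harmonic and 0.97 → 0.65 → 0.56 with dummies.

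**Reading B: the arms share a pre-trend.** The between-arm difference is then flat before the interruption. Up to a common scale, at ρ = 0:

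- Var(level) = Var(month 24) = 1/n + 0.157, so the SE is √0.240 = 0.490, √0.198 = 0.445 (−9%) and √0.184 = 0.429 (−12%) for n = 12, 24 and 36.
- Var(trend difference) = 1/1150, so the SE is 0.029 whatever n is.

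**Two limits under Reading A.**

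- Two of the three outcomes are measured over twelve months. If they are computed as overlapping monthly windows (an assumption) and fitted by ordinary least squares, the month-24 SE ratio is 0.72 at 24 and 0.55 at 36 months. The level SE does not fall; its ratio is about 1.14.
- If between-centre variance of the effect is 25% of the 12-month error variance (an assumption), the month-24 ratio at 36 months is √((0.628 + 1.581)/(6.326 + 1.581)) = 0.53 at ρ = 0, not 0.32.

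**The case against.** The strongest objection is that Reading A treats each arm's own extrapolated trend as the counterfactual, whereas this design has randomised concurrent controls and assesses differences between conditions. If the mixed model assumes a common pre-trend, which randomisation supports in expectation, the controls do most of the work and the gain is the roughly 10% of Reading B. This stands: the article does not say whether pre-trends are arm-specific. Against it, the power statement itself names level and trend changes, and nine centres are too few to rely on randomisation to balance trends.

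A reader might infer that season and trend cannot be separated in the planned analysis. That goes too far. With a harmonic they are estimable, though imprecisely; the 24 later months also inform the seasonal pattern if it is stable; and season common to both arms cancels in the contrast.

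A reader might also see a self-contradiction, because the Discussion says "previous studies have lacked enough repeated observations to adequately describe trends in outcomes". That remark concerns the number of repeated observations in other studies, and 36 in total do not clearly breach it.

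Finally, low cost is an inference from easy retrieval, since neither look-back nor price is given. The Background mentions recent primary care reforms, so older months may not follow the same line. Both points stand as conditions on the fix.

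**Conclusion.** The point holds as a cheap improvement to a stated design number, not as an error that invalidates the trial. With arm- or centre-specific pre-trends, 24 post points and ρ from 0 to 0.3, extending the baseline to 24–36 months cuts the SE of the trend change and month-24 effect by about 50 to 70% and that of the level change by about 20 to 30%. With a shared pre-trend, the month-24 and level SEs fall by about 10 to 13% at most and the trend-difference SE not at all.

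A reader might conclude that the SE of the intervention effect would be halved without qualification. The documents do not support that: it fails for the level change under either reading, depends on an unstated modelling choice for the rest, shrinks if the twelve-month outcomes use overlapping windows, and leaves between-centre variation untouched. Nor does a longer baseline rescue the power figure: with 36 baseline months at ρ = 0, power for a 0.5 SD level change in one series is still only about 16%.

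**What to change.** Replace the 12 baseline months with at least 24, preferably 36, monthly points before the interruption for every centre in both arms, as far as the databases allow (36 + 24 = 60 points). Most of the gain already arrives at 24. Before fixing the length, check the series for changes in coding or service organisation; if one is found, shorten the baseline equally in both arms.

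The cost is a longer retrospective extract and that check. Overlapping twelve-month windows would need 11 further months of records, about 47 for 36 points. No additional centres or follow-up are needed. The main downside is that older months may contain such breaks. The basis for the power claim needs separate attention.
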